## Abstract

**Background:**

Exercise has a beta cell preserving effect in patients with type 2 diabetes. This benefit of exercise has not been examined in type 1 diabetes. Significant beta cell function is present at the time of diagnosis of type 1 diabetes and therefore studies of beta cell preservation are ideally conducted immediately after diagnosis.

Many of the variables required to design and power such a study are currently unknown. The aim of EXTOD is to obtain the information required to design a formal study of exercise and beta cell preservation in newly diagnosed patients with type 1 diabetes.

**Methods:**

Barriers to exercise will initially be assessed in a qualitative study of newly diagnosed patients. Then, sixty newly diagnosed adult type 1 diabetes patients will be randomized to either conventional treatment or exercise, stratified on beta cell function and fitness. The exercise group will be encouraged to increase their level of activity to a minimum of 150 minutes of moderate to vigorous intensity exercise per week, aiming for 240 minutes per week of exercise for 12 months. Beta cell function will be measured by meal-stimulated C peptide. Primary outcomes are recruitment, adherence to exercise, loss to follow-up, and exercise levels in the non-intervention arm (contamination). The secondary outcome of the study is rate of loss of beta cell function.

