#### Randomization

Randomization will be done according to computer-generated allocation. Patients will be assigned, in a 1:1 ratio, to ‘usual care’ or ‘exercise intervention’. Allocations will remain concealed by the trial coordinator until the patients attends visit 4 when they will be randomized using on-line software. Randomization will be minimized by center, meal-stimulated 90-minute C peptide, and fitness. Due to the nature of the intervention, blinding of the study team to the randomization arm is not possible.

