### Planned sample size and analyses

A minimum of 30 patients per arm is considered sufficient to provide meaningful data to be obtained from this pilot study, but this will be reconsidered in the light of information gathered in phase 1. An initial recruitment rate of 30% is anticipated followed by a 90% adherence rate to the exercise schedule and a 15% drop-out rate. In order to complete the pilot study with a minimum of 30 patients, this means that 30/(0.85 × 0.9 × 0.3) = 130 patients will need to be approached initially.

With the varying sample sizes described above, estimates and 95% confidence intervals on recruitment rate, exercise adherence rate and drop-out rate will be:

Recruitment rate 30% (22% to 39%)

Adherence rate 90% (76% to 97%)

Drop-out rate 15% (5% to 30%)

Summary statistics (mean, standard deviation (SD), median, interquartile range (IQR), proportions) of demographic and primary outcome variables will be presented separately for intervention and control patients. Also, separately for intervention and control patients, change from baseline to 12 months in fitness related variables listed in Tables 3 and 4 will be estimated together with 95% confidence intervals. Trends over time in fitness related variables will be illustrated graphically. Variability in these changes will also be estimated in order to be able to estimate sample size requirements for a definitive trial. Comparison between intervention and control patients in change from baseline in fitness related variables will be made giving effect size estimates for the definitive trial. Association between fitness and demographic variables will be examined at a preliminary level using correlation analysis and chi-squared. A generalized linear model (GLM) will be used to get an initial impression of significance of differences between intervention and control groups in fitness related variables. Demographic variables and baseline fitness variable levels will be included as covariates. Further analysis will use non-linear mixed model analysis for outcome related fitness variables measures including the 19 sites as a random effect. Variation from site to site will then be used to further assist in the design of the definitive trial. The effect of demographic variables will also be investigated with mixed effect modeling.

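### The sixty patients to be randomized and the sample size section's 30 completers are not on one basis, and no reading of the formula leads to sixty.

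*Protocol article*

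**What the plan says.** The Methods paragraph of the abstract says that "sixty newly diagnosed adult type 1 diabetes patients will be randomized to either conventional treatment or exercise". The Randomization section adds that "Patients will be assigned, in a 1:1 ratio, to ‘usual care’ or ‘exercise intervention", so sixty means 30 in each arm.

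The section on planned sample size and analyses makes four statements:

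- On adequacy: "A minimum of 30 patients per arm is considered sufficient to provide meaningful data to be obtained from this pilot study". It does not say whether the 30 are counted at randomization or at 12 months. It adds that the number will be looked at again once phase 1 has reported.
- On the planning rates: "An initial recruitment rate of 30% is anticipated followed by a 90% adherence rate to the exercise schedule and a 15% drop-out rate".
- On the target of the calculation, it begins "In order to complete the pilot study with a minimum of 30 patients" and concludes "30/(0.85 × 0.9 × 0.3) = 130 patients will need to be approached initially". Here the 30 is a number completing, but the section does not say whether it is per arm or in total.
- On precision, it gives 95% intervals of 22% to 39% for recruitment, 76% to 97% for adherence and 5% to 30% for drop-out.

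**The concern.** The number 30 has two roles. In the abstract it is, in effect, the number randomized to each arm, because sixty is exactly 2 × 30 with no allowance for losses. In the sample size formula it is what remains after drop-out and non-adherence have been taken off. A reader cannot tell which count the minimum refers to, or whether the formula plans one group of 30 or two.

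This matters because the pilot exists to supply design inputs for a definitive trial. Change from baseline to 12 months, its variability, the between-arm effect size and the rate of loss of beta cell function all depend on patients with 12-month data. Someone who takes 30 per arm from the abstract would expect more 12-month data than the plan's own drop-out rate allows. The number to approach and the printed intervals also describe a study of a different size from the one in the abstract.

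**Working it through.** **Inputs.** Sixty randomized (abstract); 1:1 allocation (Randomization); 30% recruitment, 90% adherence, 15% drop-out, target 30 and 130 to approach (planned sample size and analyses).

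**1. Reproduce the plan's figure.** 30/(0.85 × 0.9 × 0.3) = 30/0.2295 = 130.7. The printed 130 reproduces, apart from rounding down.

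**2. Follow the formula's chain forward.**

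- Recruited: 130 × 0.3 = 39
- Adherent: 39 × 0.9 = 35.1
- Completing: 35.1 × 0.85 = 29.8

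The chain describes one group that ends at about 30.

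**3. See which denominators the printed intervals use** (exact Clopper-Pearson).

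| Rate | Printed | Chain's counts | Sixty randomized |
|---|---|---|---|
| Recruitment | 22% to 39% | 39/130: 22.3% to 38.7% | 60/200: 23.7% to 36.9% |
| Adherence | 76% to 97% | 35/39: 75.8% to 97.1% | 54/60: 79.5% to 96.2% |
| Drop-out | 5% to 30% | 5/35: 4.8% to 30.3% | 9/60: 7.1% to 26.6% |

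The printed intervals match the chain's 130, 39 and 35. They do not match sixty.

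**4. Try each meaning of 30.**

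- *30 per arm at 12 months, drop-out only.* Sixty randomized leaves 60 × 0.85 = 51, or 25.5 per arm, which is 15% below 30. To reach 30 per arm would take 30/0.85 = 35.3, so 36 per arm or 72 in total.
- *30 per arm at 12 months, net of adherence as in the formula.* Sixty leaves 60 × 0.85 × 0.9 = 45.9, or about 23 per arm. To reach 30 per arm would take 30/(0.85 × 0.9) = 39.2, so 40 per arm or 80 in total. The number to approach would be 60/0.2295 = 261.4, so 262, not 130.
- *30 in total completing.* There is no shortfall, since 51 exceeds 30. But the formula then implies 39 randomized rather than sixty, and about 15 completing per arm.
- *30 per arm randomized.* This agrees with the abstract. The number to approach is then 60/0.3 = 200, and dividing 30 by 0.85 and 0.9 has no place in the calculation.

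No reading makes the abstract, the formula and the intervals agree.

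**The case against.** The strongest reply is that nothing in the article sets a minimum of 30 per arm completing. A reader might infer one by taking "per arm" from one sentence and completion from another, but the text does not join them. Read literally, 30 per arm could be the number randomized, which matches sixty exactly, and 30 completing could be a total, which 51 exceeds. This stands. The article does not establish a shortfall against a stated completer target.

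The reply does not clear the plan, however. On that reading the formula recruits 39, not sixty, and the intervals are those of the smaller study.

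Three further points have weight:

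- The section calls 30 per arm a minimum and leaves it open to review after phase 1. A reader might infer that recruitment must stop at sixty, but the article does not say so. The review clause allows a later change; it does not reconcile the present figures.
- The primary outcomes are recruitment, adherence, loss to follow-up and contamination. Drop-out is itself being estimated, and beta cell loss is secondary. This limits the consequence.
- The article states no power, so no loss of power can be charged against it.

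**Conclusion.** The point holds as an inconsistency in the basis of the sample size, not as proof that a stated completer target is missed. On the plan's own 15% drop-out, sixty randomized gives about 51 patients with 12-month data (25 to 26 per arm), or about 46 if the 90% adherence factor also removes patients. The number to approach is 130 by the formula but 200 for sixty randomized at 30% recruitment. The printed adherence and drop-out intervals rest on 39 and 35 patients.

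These figures assume that the three planning rates apply as stated and that drop-out is equal in the two arms. The 46 also assumes, as the formula does, that adherence is applied to everyone recruited. The plan should be corrected, because its 12-month data and its stated precision are meant to feed the definitive trial. For a pilot with feasibility outcomes, the consequence is moderate.

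**What to change.** In the section on planned sample size, state that 30 per arm (60 in total) is the number randomized, and that at 15% drop-out about 51 patients (25 to 26 per arm) are expected to give 12-month data. State also whether patients who do not adhere but are followed up count as completing.

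Then put the other figures on the same basis:

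- Number to approach: 60/0.3 = 200, replacing 130.
- Recruitment interval, exact, 60/200: 24% to 37%.
- Drop-out interval, exact, 9/60: 7% to 27%.
- Adherence interval, on the exercise arm only because the schedule applies only there, exact, 27/30: 73% to 98%.

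Keep the provision to reconsider the size after phase 1, and say which of these counts it would change.

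The cost is rewording and a short recalculation, with no additional randomized patients. The expected number with 12-month data will look less favourable, the adherence interval widens slightly, and the number to approach rises on paper from 130 to 200.

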**Discussion:**

The outcomes of the EXTOD study will help define the barriers, uptake and benefits of exercise in adults newly diagnosed with type 1 diabetes. This information will enable design of a formal study to assess the effect of exercise on beta cell preservation in newly diagnosed patients with type 1 diabetes.

**Trial registration:**

Current controlled trials ISRCTN91388505

## Background

### The natural history of beta cell loss in type 1 diabetes

Type 1 diabetes (T1DM) is a chronic inflammatory autoimmune disease characterized by destruction of insulin producing beta cells and by subsequent insulin deficiency [1]. It affects 0.3% of the UK population, approximately 250,000 people, and its incidence is rising [2]. In the UK, it has been reported to result in a shortening of life expectancy by over 20 years [3].

The loss of beta cells that results in T1DM is a gradual process, and between 50 and 25% of beta cell function can be present at the time of diagnosis [4]. However this residual function is insufficient to generate the insulin required for metabolic control, and the lack of insulin results in a number of metabolic derangements which if untreated results in death. Patients with T1DM therefore start insulin injection replacement therapy at diagnosis. It has generally been assumed that the remaining beta cells are rapidly and completely destroyed soon after diagnosis. However, recent studies indicate that these cells can persist for over 50 years following diagnosis [5-7], and that their presence is associated with important clinical benefits. These benefits include improved glucose control, reduced retinopathy and nephropathy, and with more than a halving of rates of hypoglycemia [8-11]. These benefits of preservation of beta cell function are significant, and the FDA (USA), and EMEA (Europe) state that even partial preservation of beta cell function ((estimated by a stimulated C peptide > 200 pmol/L - elaborated below)) is a sufficient basis for the licensing of new therapies for T1DM [12].

### What are the benefits of beta cell preservation in people with type 1 diabetes?

Whilst beta cell mass cannot be directly measured, it can be accurately estimated through measurement of stimulated C peptide (a component of the pre-insulin molecule) following a physiological meal stimulus [13]. Meal-stimulated C peptide provides an acceptably accurate estimate of beta cell function for use in studies of beta cell preservation [14]. A meal-stimulated C peptide value of greater than 200 pmol/L is associated with the clinical benefits outlined above. C peptide assay technology has improved over the recent years, and through National Institute of Diabetes and Digestive and Kidney Diseases (NIDDK) sponsored standardization workshops, levels of 30 pmol/L can now be measured reliably and reproducibly across different laboratories [15]. More recently, the development of sensitive assays has allowed C peptide detection down to levels of 1.5 pmol/L [16]. Such assays have provided even stronger support for the persistence of beta cell function in people with long standing T1DM, albeit at levels that do not provide independence from insulin injections [17]. Current estimates therefore are that 60% of subjects will have a stimulated C peptide greater than 200 pmol/L at two years following diagnosis, but that C peptide is detectable at lower levels in 64% of people at 50 years after diagnosis [7].

### How can we preserve beta cell function in people with type 1 diabetes?

A number of medicinal products are currently under investigation for the preservation of beta cell function in subjects newly diagnosed with T1DM. They are largely immunomodulatory agents that act by ‘suppressing’ the inflammatory autoimmune process targeting the beta cell. Whilst some of them act to modulate the autoimmune process specifically against beta cell antigens [18], others act through broad, non-antigen specific immune suppression [19]. Many of these therapies are associated with significant risk of side effects. These include infection or reactivation of latent infection, inflammation at the sites of injection, and the risk of cancer and infection associated with immunosuppressive therapy [20]. Furthermore, these new therapies have yet to demonstrate significant and sustained benefit. Whilst we clearly need to continue investigating such novel therapies, there is also a pressing need to examine new therapies with an acceptable side effect profile, and which potentially could be used as an adjunct to the medicinal products under investigation. We are interested in the role of exercise in this regard.

### Can exercise preserve beta cell function in people with type 1 diabetes?

Exercise has been demonstrated to preserve beta cells in animal studies [21-23]. Pancreatic sections from a rat model of insulin deficient diabetes revealed a 33% increase in staining for beta cells, and a 31% increase in beta cell mass following an eight-week exercise program. The mechanisms underlying this effect remain unclear but a significant decease in beta cell apoptosis was reported [24]. Exercise has a recognized anti-inflammatory effect [25] that may therefore modulate the autoimmune process against the islet.

These beneficial effects of exercise on beta cell function have also been demonstrated in healthy human subjects [26], and in the context of people with pre- or established type 2 diabetes [27,28]. Here also, the exercise has been of vigorous intensity with a VO2max of 70%, and of sustained duration. The disposition index used in this study as an estimate of beta cell function, revealed a 27% improvement following a one-week program of exercise in older people with impaired glucose tolerance [27]. More recently, an eight-month exercise program in middle-aged overweight people revealed a 60% improvement in beta cell function and a 20% improvement in insulin resistance with moderate intensity exercise (walking at a slow pace for 60 minutes on three days per week) [29].

Until recently, many observers have remained skeptical that increases in exercise can be maintained long enough to have any significant impact on diabetes risk or help improve diabetes management. However, large intervention studies targeting subjects with impaired glucose tolerance have demonstrated that a program of lifestyle changes focusing on improved diet and increased exercise is able to delay or possibly prevent the development of type 2 diabetes mellitus (T2DM) over a period of four years [30,31]. Both studies found lifestyle intervention to result in a 58% reduction in the incidence of diabetes, irrespective of age. Importantly, both studies also showed that it was possible to maintain increased levels of exercise for four years. Furthermore, we ourselves have shown that a program of lifestyle changes focusing on improved diet and increased exercise, reduces insulin resistance, weight, and drug usage and improves diabetes control in newly diagnosed type 2 patients [32]. In this study, we demonstrated that with a simple home-based, ‘unsupervised’ and relatively inexpensive exercise regime we can maintain increased levels of exercise for 12 months.

We therefore believe that regular exercise, if demonstrated to show benefit in patients with residual beta cell function, can be undertaken and maintained by patients with diabetes.

### Hypothesis

Our hypothesis is that exercise preserves beta cell function in people with T1DM. We base this hypothesis on previous studies of exercise in T2DM, pre-T2DM, and people without diabetes, where exercise is associated with preservation of beta cell function.

### Research goals

In order to test our hypothesis, we will initially undertake a qualitative study to identify barriers to the uptake and adherence to an intensive exercise program, and determine the most acceptable way to monitor exercise levels. We will then undertake a pilot RCT involving an exercise intervention in patients with recent onset T1DM in order to:

1) Determine the proportion and characteristics of patients with T1DM who would be willing to take part in an RCT of exercise (that is, recruitment rate).

2) Define the rates of exercise adherence to the intervention and participant drop-out. The unsupervised exercise program will aim to encourage patients to safely increase and maintain their exercise level to at least 150 minutes per week, and aiming for 240 minutes per week of vigorous intensity exercise. A minimum level of 150 minutes per week is recommended by major diabetes organizations [33,34]. However, to maximize the chances of seeing a benefit in beta cell function, patients will be encouraged to aim for 240 minutes per week.

3) Determine the rate of exercise uptake in the non-intervention arm (that is, intervention contamination). This issue is important because it has the potential to dilute trial effects, and adjustments for this will need to be made when calculating the sample size for a definitive trial.

4) Determine the rate of loss of beta cell function (potential effect size) in the intervention and control arm to enable the statistical power calculations for the subsequent definitive trial to be refined.

5) Determine (as a secondary outcome) whether the 12 months exercise intervention results in a significant preservation of beta cell function.

## Methods and design

### Setting and recruitment

The study will take place across 19 NHS hospital Trusts in the UK: University Hospital Birmingham, Taunton and Somerset, University Hospitals Bristol, North Bristol, Gloucester Hospitals, Yeovil District Hospitals, East and North Hertfordshire, Mid Yorkshire Hospitals, Oxford University Hospitals, Worcestershire Acute Hospitals, George Eliot Hospital, The Dudley Group, Walsall Healthcare, The Royal Wolverhampton Hospitals, Heart of England, Sandwell and West Birmingham, Weston Area Health, Royal United Hospital Bath and Royal Devon and Exeter Hospital. Recruitment will focus on NHS hospital trusts as the vast majority of patients newly diagnosed with T1DM are referred to hospital for initiation of insulin.

### Participant selection

Clinical staff at participating hospitals will identify patients newly diagnosed with T1DM. They will approach these patients about the study and ask permission for their contact details to be forwarded to the EXTOD study team. Interested participants will then be contacted by the study team by telephone and invited to attend their local study centre for a screening visit. At the first visit written informed consent will be obtained by a member of the study team (physician or research nurse). Patients will be considered eligible for enrollment in this trial if they fulfill all the inclusion criteria and none of the exclusion criteria (see Table 1).

**Table 1 T1:** Inclusion and exclusion criteria

**Inclusion criteria**	Aged 16 to 60
	Diagnosed with T1DM within the previous 12 weeks
	Able and safe to exercise (as determined by the lead physician)
	Willing to self-monitor and record blood glucose levels
	Willing to take insulin as part of a multiple dose injection regime
	Feel able to increase their current levels of exercise
	Have a meal-stimulated C peptide value greater than 200 pmol/l (these criteria are not required for recruitment into phase 1)
**Exclusion criteria**	Psychological or physical disease that prevents exercise
	Concomitant therapy that affects heart rate (for example, beta blocker, calcium channel antagonist) as we would be unable to monitor their exercise adherence
	Major surgery or other planned event that would prevent exercise for more than six weeks
	Pregnancy or planning pregnancy
	Uncontrolled blood pressure (greater than 180/100 mmHg), as it is unsafe to exercise with this blood pressure

### Study design

The EXTOD study is designed in two phases. Phase 1 is a qualitative study designed to inform on the most feasible and patient-friendly way of motivating patients newly diagnosed with T1DM to undertake and maintain a graded exercise program, and to determine the most acceptable way to monitor exercise levels. This understanding is essential for the conduct of phase 2.

Phase 2 is a pilot RCT to assess uptake, intervention adherence, drop-out rates, and rate of uptake in the usual care group during a 12 month exercise intervention, and the effect of this intervention on beta cell function.

